A few clinical trials looked at effects of MBIs on self-control as assessed with neurocognitive tests and/or with questionnaires in youth with ADHD. In a first RCT, comparing a family MBI with a waitlist control group in children with ADHD aged five to seven years (*N* = 100) and their parents, significantly greater improvement in the family MBI group compared to control group was found for child executive attention (conflict monitoring)(d = .41) [52]. This result is in line with a quasi-experimental trial on neurocognitive task performance following an MBI in adolescents (*N* = 8) and adults (*N* = 24) with ADHD, which also found significant improvements for measures of executive attention. In addition, significant effects were found for set-shifting [53]. A pilot pre-post-intervention study with a family MBI in children aged eight to twelve years (*n* = 11) found significant improvement with large effect sizes on objective attention tests, but not on parent ratings of self-control on the Behaviour Rating Inventory of Executive Function (BRIEF) [54]. In contrast, in a quasi-experimental trial with ten adolescents (aged 11–15 years) following a family MBI, self-control assessed with the BRIEF improved significantly at 8-weeks follow-up, but only according to father reports and not mother reports [55]. For youth with ADHD, no RCT has been published on effects of MBIs on ecologically valid questionnaire ratings of self-control (e.g. BRIEF). In adults with ADHD, a randomised waitlist controlled MBI trial (*N* = 20) resulted in significant group differences at the end of treatment favouring the MBI group on self-reported self-control (assessed in the laboratory and with ecological momentary assessment) and clinician rated self-control with large effect sizes. In contrast, no significant improvement was observed with the objective self-control tasks [56]. In another waitlist RCT on an MBI in adults with ADHD (*N* = 103), self-control as assessed with the BRIEF improved with a large effect size (d = .93) as well [57]. Furthermore, in a randomised CAU controlled MBI trial in 120 adults with ADHD, improvement on the BRIEF over time after MBI + CAU compared with CAU only was found, resulting in an effect size of d = .49 at 6-month follow-up [58]. In summary, implementing MBIs in the treatment of youth with ADHD to improve self-control is promising. Although there are preliminary positive results, the existing evidence in youth is insufficient due to a lack of studies with good methodological quality. RCTs with sufficient power are needed.

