### Sample size

#### Power calculation

Power analyses are based on the primary hypothesis that family MBI, relative to control, will lead to improvement in self-control (as measured by the BRIEF) at end of treatment. The BRIEF has shown modest to large effect sizes in MBI studies for clinical samples, including bipolar disorder [140][Cohen’s d effect sizes from 0.08–1.33 on self-report BRIEF] and adult ADHD [57][Cohen’s d effect size from 0.43 to 0.93 on self-report BRIEF]; [56][Cohen’s d effect size from 0.67 to 1.72 on self-report BRIEF]. Further, in previous work using the MYmind programme (unpublished data on a larger non-randomised waitlist-controlled pilot in youth with ADHD *N* = 195 families using parent-report BRIEF; see also [55][Cohen’s d effect size from 0.0 to 1.8 on parent-report BRIEF; 0.2 to 0.5 on teacher-rated BRIEF]), a moderate effect on the BRIEF was found. Therefore power calculations were based on a moderate effect size of 0.4. Power analyses were run using the software G*power 3.1 and based on the procedure by G. F. Borm, J. Fransen and W. A. Lemmens [141]. Using this method, the N per group is obtained from the N per group for t-test multiplied by the design factor (D). The design factor D = 1–r^2^, where r^2^ is the correlation between baseline and end of treatment on the BRIEF. We determined r using the data of a normative sample over a comparable time frame (six weeks): .86 [142]. As the period between baseline and end of treatment is slightly longer in this trial (around eleven weeks) the power analyses was conducted using a more conservative estimate of *r* = .76, hence D = 1–.76^2^ = .42.

Based on a power of 80%, a two-tailed test with α = .05 and an estimated effect size of 0.4, we need 100*.42 = 42 children in each group. Past studies conducted using the MYmind programme (see section *Intervention*) using non-randomised designs in youth with ADHD and ASD found attrition rates from 5 to 15%. Therefore, we will recruit a slightly larger sample (2xN = 50, total *N* = 100), allowing room for attrition of around 15%.

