### Statistical analyses

Data will be analysed and reported according to CONSORT guidelines. Baseline demographic and clinical characteristics of the family MBI- and CAU-groups will be compared to examine whether these have been distributed evenly across the two groups by the randomisation. The primary analyses will be aimed at comparing results on the outcome measures at end of treatment between the family MBI and CAU condition, controlling for baseline levels and possible other baseline differences between intervention and CAU groups. To test our primary hypothesis that assignment to family MBI (relative to CAU) will improve child self-control, we will use ANCOVA with group condition (family MBI versus CAU) as the primary independent variable, and child self-control (continuous BRIEF-P score) at end of treatment as the primary dependent variable and child self-control at baseline as covariate. Cohen’s d effect sizes will be calculated. Analyses will be conducted both according to intention-to-treat principle, and per-protocol on completers (family MBI condition: child and parent attended > = 4 family MBI sessions). Intention-to-treat analyses will be conducted using available case analysis (not considering individuals with missing data) as well as imputation, as described in [145]. In case both parents participate in the assessments, data of the parent with the most complete dataset will be used for the ANCOVA, and if both are complete, the sex of the parent (or age, for same-sex parents) will determine which dataset will be used so that the fathers:mothers ratio is most similar across both study arms.

Secondary analyses, aimed at examining the consolidation of treatment effects at follow-ups, will use multilevel modelling with time point as repeated measurement, following the approach described in [58]. Moreover, we will conduct a set of complementary analyses to derive prediction models for response to intervention from baseline characteristics, and explore interactions between child and parental outcomes.

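### In two-parent families the primary BRIEF-P rater is chosen by data completeness after randomisation, then by a father:mother ratio target that does not fix one dataset

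*Protocol article*

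**What the plan says.** The Eligibility criteria ask for at least one participating parent, so a child may have one or two raters. The Primary outcome measure section specifies the parent-rated BRIEF without naming which parent rates.

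The choice is made in Statistical analyses, in two steps. First: "In case both parents participate in the assessments, data of the parent with the most complete dataset will be used for the ANCOVA". Second, where both are complete, the parent's sex (age, for same-sex parents) "will determine which dataset will be used so that the fathers:mothers ratio is most similar across both study arms".

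The section does not say when the choice is made, in what order families are taken, or whether the person choosing is blind to BRIEF scores. It does not say whether completeness refers to BRIEF-P at baseline and end of treatment or to everything a parent fills in up to the 6-month follow-up. Two parents who are equally incomplete fall under neither step.

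**The concern.** There are two separate difficulties.

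**A selection variable that arises after randomisation.** A parent's completeness becomes known during follow-up. In the family MBI arm parents attend eight weekly sessions and a booster and do daily homework; in the care-as-usual arm they do not. Whether a parent keeps completing questionnaires may therefore depend on allocation, and the type of parent who becomes the rater may differ between arms. Parents are not blinded: the blinding measures in the protocol concern teachers. Matching on parent sex does not balance engagement or expectancy.

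**A target in place of an assignment rule.** A ratio that should be as similar as possible across arms can be met by many different sets of families. Checking it needs the final data and the allocation of both arms. Two analysts who follow the text faithfully could arrive at different primary datasets and different estimates.

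At stake is which score enters the single primary test for these children.

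**Working it through.** **Step 1. The plan's own sample size.** Inputs from Power calculation: "a two-tailed test with α = .05 and an estimated effect size of 0.4", 80% power, "hence D = 1–.76^2^ = .42".
- Two-sample t-test: 99.08 per group.
- Design factor: 1 − 0.76² = 0.4224.
- 99.08 × 0.4224 = 41.9, rounded up to 42. This agrees with "we need 100*.42 = 42 children in each group".
- 42 / (1 − 0.15) = 49.4, rounded up to 50 per group, as planned.

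The sample size reproduces and does not depend on how the rater is chosen.

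**Step 2. How many datasets meet the ratio target.** The protocol does not give the number of families with two complete raters, so this is shown over a range (assumption). Within one arm, if j of k such families are to supply the father, C(k, j) selections comply: C(12, 3) = 220 and C(20, 5) = 15,504. Over both arms, with k such families in each and half supplying the father (rounded down when k is odd), the count is C(k, j)²:
- k = 5: 10² = 100
- k = 10: 252² = 63,504
- k = 15: 6,435² = 41,409,225

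All selections in a row give the same ratio in both arms, provided the remaining families have the same mix. These counts show that the rule is indeterminate. They do not measure bias or error.

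**Step 3. What this does to type I error.** Null simulation of the ANCOVA with 42 children per arm, baseline-to-end correlation 0.76 and 1,000 runs per row. The inter-parent correlation and k are assumptions. The Monte Carlo standard error at 5% is √(0.05 × 0.95 / 1000) = 0.007.

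| Inter-parent correlation | k per arm | Error, one arbitrary pick | Error, smallest p of 20 compliant picks | Mean range of estimate over 20 picks (SD) |
|---|---|---|---|---|
| 0.4 | 10 | 0.063 | 0.139 | 0.137 |
| 0.4 | 20 | 0.044 | 0.191 | 0.199 |
| 0.6 | 10 | 0.058 | 0.125 | 0.115 |
| 0.6 | 20 | 0.045 | 0.143 | 0.163 |
| 0.8 | 10 | 0.051 | 0.085 | 0.080 |
| 0.8 | 20 | 0.055 | 0.118 | 0.116 |

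One pick made without regard to the scores stays near 5%. The fifth column shows why the estimate is still not reproducible: compliant choices differ by 0.08 to 0.20 SD on average, against a planned effect of 0.4.

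**Step 4. Bias from the completeness step.** Bias = (difference in treatment effect between rater types) × (net share of the arm whose rater type is shifted by allocation). The protocol gives neither term. As an illustration, assume a difference of 0.3 SD, 40% of families with two raters, and unequal completeness in 25% of those. At most 0.40 × 0.25 = 10% of the arm is affected. Even if every such choice shifts the same way, the bias is 0.3 × 0.10 = 0.03 SD, or 0.03 / 0.4 = 7.5% of the planned effect. Shifts of 20 to 30 points over the whole arm would give 0.06 to 0.09 SD (15% to 22.5%), but that requires many more affected families.

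**The case against.** The rule is stated in advance, applies in the same form to both arms and uses no BRIEF values. The text does not say that the choice is made with scores in view; that it comes after follow-up is inferred from what the rule needs. A tie-break algorithm and its blinding may stand in a full protocol or analysis plan that is not shown. Data collection also limits differences in completeness: items cannot be skipped, non-responders are reminded and telephoned, and those who stop are offered a drop-out questionnaire that includes BRIEF-P. All of this stands, and it keeps the point modest. It does not answer the first step: completeness is the stated criterion, not an omitted detail. Forced item completion also makes ties likelier, so the undefined second step may decide more often.

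A reader might infer more than the documents support:
- **That type I error is inflated.** Step 3 shows 8.5% to 19% only if someone takes the smallest p-value among 20 selections. Nothing in the protocol suggests that this will be done.
- **That father or mother as rater decides the result.** The Background reports a BRIEF improvement "but only according to father reports and not mother reports", but from a quasi-experimental study of ten adolescents at 8-week follow-up, whereas the primary endpoint here is end of treatment. Significance in one rater group and not the other, at that size, does not show that effects differ. Parent sex is also exactly what the ratio step balances.
- **That care-as-usual families escape selection.** The same rule applies to them, and their parents can differ in completeness too.
- **That the second parent's data are thrown away.** The rule is limited to the ANCOVA.

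**Conclusion.** The point holds in a limited form. In families with two raters, the primary informant depends on a variable measured after randomisation that allocation may affect. Where both raters are complete, the text does not identify one primary dataset. This is an avoidable opening for selection bias and a lack of reproducibility in the primary analysis. It is not evidence of a biased or anti-conservative test.

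Its size cannot be taken from the document: the number of two-parent families, the inter-parent agreement and any difference in completeness between arms are all unstated. The 0.03 SD illustration, the larger 0.06 to 0.09 SD figures and the simulation ranges all rest on the assumptions given with them. If an analysis plan outside this review fixes a blinded, deterministic tie-break, the second difficulty falls away and the first remains.

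**What to change.** Record one primary informant per child on the consent forms, before randomisation. Baseline is too late: randomisation follows completion of the consent forms, and Procedure and treatment allocation provides for undoing it if a family withdraws before the baseline assessments, so allocation already exists at T0. Use that parent's BRIEF-P at all time points in the ANCOVA whatever its completeness, and impute where missing; the plan already includes an imputed intention-to-treat analysis.

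For families already enrolled, apply a deterministic rule that uses only facts fixed before randomisation, or a seeded random pick made blind to allocation and scores. Write it down before outcome data are examined by arm.

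Use the second parent's ratings as an auxiliary variable in the imputation, and in a sensitivity mixed model with ratings nested within child.

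The cost is one field at consent and a few sentences of analysis text. The drawback is that some primary-informant values will be missing where the present rule would have substituted the other parent; these must be imputed and will drop out of the available-case analysis. The sample size stays at 42 per group, or 50 with attrition.

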
The current protocol describes an RCT comparing an 8-week family MBI for youth with ADHD and their parents (MYmind) in addition to CAU with continuation of CAU only. Participating children will have an ADHD diagnosis and comorbidities will be allowed (including ASD). The primary, secondary and tertiary aims correspond to the primary, secondary and tertiary measures that will be used in this study. The primary aim is to investigate the effectiveness of a family MBI in improving self-control of youth with ADHD, as assessed with ecologically valid parent-ratings (BRIEF-P, primary outcome). Different definitions are used in literature on self-control, some take a broad approach, other narrow, and opinions vary on what self-control comprises. We take a broad view on self-control in that it entails self-regulation of behaviour, emotion, cognition and attention. Given the moderate convergent validity of neurocognitive tests of self-control, we prefer ecologically-valid questionnaire ratings of self-control over neurocognitive tests [2]. The predictive validity of behavioural questionnaire ratings of self-control on clinically and societally relevant objective outcomes even decades later (e.g. months unemployed, single parenthood, criminal conviction) has been documented [1, 59]. The secondary aim is to examine the effects of family MBI on child self-control as assessed with teacher-ratings (BRIEF-T) and objective computerised tasks and on psychological symptoms (e.g. ADHD symptoms, symptoms of ASD, brooding), well-being and mindfulness of the children (secondary outcome measures for children). In addition, we aim to examine effects of family MBI on parental self-control as assessed with ecologically valid self-ratings (BRIEF-A) and objective computerised tasks and on psychological symptoms, well-being and mindful parenting of the parents (secondary outcome measures for parents). Our tertiary aim is to look at the effects of family MBI on some exploratory measures such as mind-wandering. Finally, child saliva samples will be collected for (epi)genetic research and qualitative data will be collected to explore effects that are not captured with quantitative assessments and to explore facilitators and barriers of family MBI for youth with ADHD and their parents.

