### Participants

The study population will consist of children aged 8–16 years with an ADHD diagnosis and at least one of their parents. The families will be recruited through the outpatient clinic of Karakter, an institute for child and adolescent psychiatry. Recruitment will take place at three different Karakter locations in the central eastern part of the Netherlands, namely Nijmegen, Arnhem and Ede (see also the clinical trial registration). In addition, families will be recruited by media advertisements.

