#### Eligibility criteria

We will include families who meet the following criteria: a) child is 8–16 years old and in the third grade of primary school or higher; b) child has a primary diagnosis of ADHD according to the Diagnostic and Statistical Manual of Mental Disorders (DSM-IV or DSM-5) system [60, 61] and confirmed by a structured interview (see Assessments section); c) child receives CAU for ADHD and has remaining ADHD symptoms (average score > 1.0 on the investigator-rated DSM-5 items from the Conners’ ADHD rating scale [62]); d) ADHD medication dose of child is stable, at least two weeks prior to baseline, or an informed decision is made on not taking ADHD medication; e) at least one parent is willing to participate. Exclusion criteria are a) psychosis, bipolar illness, active suicidality, untreated posttraumatic stress disorder or substance use disorder of the child that impedes functioning; b) psychosis, bipolar disorder, active suicidality, untreated posttraumatic stress disorder or substance use disorder of the parent that impedes functioning; c) child and/or participating parents have an estimated Intelligence Quotient (IQ) < 80; d) child and/or participating parents do not have adequate mastery of Dutch language; e) child and/or participating parents have participated in an > = 8-week mindfulness programme in the past year or ever in a Mindful Parenting training; f) child or parents participate in another intervention study.

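### The one-parent rule for the end-of-treatment ANCOVA makes no exception for parents' own outcomes; applied to them, it would discard a second participant's data and lose precision on secondary outcomes

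*Protocol article*

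**What the plan says.** Families enter with one parent or more. Participants describes children with "an ADHD diagnosis and at least one of their parents", and Eligibility criteria asks that "at least one parent is willing to participate". The expected share of families with two participating parents is not given.

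Parental outcomes are a declared part of the secondary aim. In Background the article says "we aim to examine effects of family MBI on parental self-control as assessed with ecologically valid self-ratings (BRIEF-A"), followed by computerised tasks, psychological symptoms, well-being and mindful parenting. Table 2 schedules these at T0, T1 and T3, and some also at T2.

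In Statistical analyses:

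- The aim at T1 is general: "The primary analyses will be aimed at comparing results on the outcome measures at end of treatment between the family MBI and CAU condition", with adjustment for baseline.
- The one ANCOVA written out takes "child self-control (continuous BRIEF-P score) at end of treatment as the primary dependent variable and child self-control at baseline as covariate".
- With two parents, "In case both parents participate in the assessments, data of the parent with the most complete dataset will be used for the ANCOVA". If both datasets are complete, the sex of the parent (age for same-sex parents) "will determine which dataset will be used so that the fathers:mothers ratio is most similar across both study arms". In either case one dataset is kept.
- Follow-up analyses "will use multilevel modelling with time point as repeated measurement, following the approach described in [58"]. Whether one parent or both enter that model is not stated.

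**The concern.** When the outcome is a rating of the child, two parents are two informants on one subject, and keeping one of them is a reasonable way to have one observation per child. This point does not dispute that.

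When the outcome is the parent's own score, the second parent is a different person with an own baseline and an own T1 value. The protocol treats parents this way elsewhere: participating parents are checked for IQ, Dutch language and earlier mindfulness training, and the intervention has a parallel parent group that also addresses the parents' own self-control. By the item counts in the outcome sections, the self-report questionnaires that Table 2 lists at T1 come to 193 items for each parent (75 + 26 + 10 + 21 + 5 + 5 + 14 + 31 + 6), besides the computerised tasks.

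Read literally, the rule would leave those data out of the T1 comparison of every parental outcome. At stake is the precision of the secondary parental results, and whether they describe all assessed parents or, in two-parent families, only the one with the more complete data.

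**Working it through.** **1. The plan's own figure.** At d = 0.4, two-sided α = .05 and 80% power, a t-test needs 100 per group. The design factor is D = 1 − .76² = .4224, and 100 × .4224 = 42.2, stated as 42. Allowing for 15% attrition, 42/0.85 = 49.4, rounded up to 50 per group. This reproduces the article. The calculation counts children and uses the child BRIEF, so the handling of a second parent's self-ratings does not enter it.

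**2. Does the rule reach the parental outcomes?** Three features of the text say yes: the T1 aim covers the outcome measures in the plural, ANCOVA is the only method named for T1, and the rule selects a parent's dataset, not a BRIEF-P score. Two features say no: the ANCOVA is spelled out only for BRIEF-P, and the rule refers to it with the definite article. The wider scope is therefore a fair inference but not a stated fact.

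**3. Size of the loss if it does.** Inputs, neither of them in the documents and so assumed:

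- f, the share of families with two participating parents;
- ρ, the within-couple correlation of the baseline-adjusted parent outcome.

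The mean of two parents has variance σ²(1+ρ)/2, against σ² for one parent. A two-parent family thus carries 2/(1+ρ) units of information, where a one-parent family carries 1. Averaged over families:

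(1 − f) + 2f/(1+ρ) = 1 + f(1−ρ)/(1+ρ).

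The one-parent rule gives 1 throughout, so the gain from using both parents is f(1−ρ)/(1+ρ):

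| f | ρ = 0.2 | ρ = 0.4 | ρ = 0.6 |
|---|---|---|---|
| 0.2 | 13.3% | 8.6% | 5.0% |
| 0.3 | 20.0% | 12.9% | 7.5% |
| 0.5 | 33.3% | 21.4% | 12.5% |
| 0.75 | 50.0% | 32.1% | 18.8% |
| 1 | 66.7% | 42.9% | 25.0% |

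For f of 0.3 to 0.5 and ρ of 0.2 to 0.4 the gain is 12.9% to 33.3%. The standard error is multiplied by 1/√1.129 = 0.94 down to 1/√1.333 = 0.87, so it is 6 to 13% smaller.

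**4. Illustration in power.** Take 42 families per arm and d = 0.4 on a parental outcome, with gains of 12.5% and 33.3%. If the child-BRIEF value D = .42 carried over to parents, power would rise from 80.5% to 84.9% and 90.3%. With no help from baseline (D = 1), it would rise from 44.9% to 49.4% and 56.2%. Neither value of D is given for parents.

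The formula assumes equal variance and equal treatment effect in both parents, and complete data from both. A less complete second parent lowers the gain.

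**The case against.** The strongest objection is scope. The only ANCOVA specified is the primary one on the child BRIEF-P. Balancing fathers and mothers across arms reads naturally as matching informants. How secondary parental outcomes are modelled may sit in a full protocol or SAP that is not shown. This stands to the extent that the wider scope must be called an inference. It does not dispose of the point, because the article states a rule with general wording and no exception; it is not simply silent.

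Second, 13 to 33% is not a property of this trial. That stands: it holds only under assumed f and ρ, and the wider grid runs from 5% to 67%.

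Third, the rule concerns parents who take part in the assessments, and nothing says that a second assessed parent also attends the parent sessions. Including non-attenders could dilute the effect on parents, so a smaller standard error need not bring more power. That stands, and the fix has to allow for it.

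Fourth, a reader might infer more than the text supports:

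- *That the primary result is biased or its test invalid.* One observation per child is a valid basis for the BRIEF-P ANCOVA, and one parent per family is a valid, if less efficient, way to avoid clustering.
- *That the parental results describe an arbitrary half of the parents.* Selection follows a stated order: completeness first, then balance of fathers and mothers.
- *That the second parent's data are never used.* The rule is tied to the ANCOVA. The article does not apply it to the follow-up multilevel model, the prediction models or the analyses relating child and parent outcomes.

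**Conclusion.** The point holds conditionally and is limited to precision. As written, the one-parent rule has no exception for parents' own outcomes. If it is applied to them, data already collected from a second participant drop out of the T1 comparison. The loss is about 13 to 33% of the information that one parent per family provides (standard errors 6 to 13% larger than need be, taken as the reduction that using both parents would bring) if f is 0.3 to 0.5 and ρ is 0.2 to 0.4. Over f of 0.2 to 1 and ρ of 0.2 to 0.6 it is 5 to 67%, and less where the second parent's data are incomplete. Only secondary parental outcomes are affected. The primary test and the sample size are not. Because the remedy is cheap and uses existing data, the change is worth making.

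**What to change.** 1. State that the one-parent rule applies only to parent-rated child outcomes.
2. For parents' own outcomes at T1, analyse every participating parent in a linear mixed model with arm, the parent's own baseline score, parent sex and a random intercept for family, using small-sample degrees of freedom.
3. Use the same family level in the T2 and T3 multilevel model, and say that both parents enter it.
4. Report a sensitivity analysis with one parent per family, or with attending parents only, to show whether second parents who were assessed but did not attend dilute the effect.

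If an SAP already says this, a sentence pointing to it is enough.

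The cost is a few lines of text and slightly more modelling. No new data, families or visits are needed, and the primary analysis stays as it is.
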